**Figure 1. F0001:**
[figure not shown]
Visual representation of study design and follow-up visits. HAM-D_17_: Hamilton Depression Rating Scale 17 item version; MDI: Major Depression Inventory; WHO-5 World Health Organization Quality of Life Index; PSQI: Pittsburg Sleep Quality Index; SIDAS: Suicidal Ideation Assessment Scale; YMRS: Young Mania Rating Scale; UKU: The UKU Side Effect Rating Scale; SCIP: The Screen for Cognitive Impairment in Psychiatry. TMT-B: Trail Making Test Part B; FERT-Facial Emotion Recognition Task; ECMT: Emotional Categorization and Memory Test; SSVEPs: Steady State Visually Evoked Potentials.

Patients are free to withdraw from the trial at any time. Drop out criteria include hospitalisation due to a somatic illness, admission to a psychiatric ward for any length of time, side effects at a level unacceptable to the subject, worsening of depression such that it would be unethical not to try other treatments, the patient or the patient’s healthcare provider changes the dose of medication affecting the depression, onset of mania assessed according to the YMRS with a score of 7 or above or fulfilling the diagnostic DSM-5 criteria for a current hypomanic or manic episode, and patients reports conditions treatment that interfere with blinding. Patients who drop out from the trial continue their treatment and follow-up care at Psychiatric Centre Copenhagen.

A GCP monitor (GCP-Unit, University of Copenhagen, Frederiksberg Hospital) has been assigned to the study and will follow the clinical trial, randomization, blinding, and data collection procedures.

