## Study design and interventions

The study is a randomized, double-blinded, placebo-controlled, single-center clinical trial investigating the effects of 40 Hz brain stimulation. Patients are randomly assigned to one of two groups: 40 Hz masked flickering white light (active) and continuous non-flickering white light matched in color temperature and brightness (placebo). This is a double-blind study, so neither the participant nor the researcher will know which treatment the participant is receiving. Both kinds of light appear as white light, so the normal white light serves as a well-matched placebo. As a precaution, the investigators doing the assessments will not see the devices turned on but will instruct the trial participants on correct device use during the baseline meeting. Each participant is handed out a user manual with detailed instructions on how to handle the light therapy and recommended daily usage times. Participants will receive in-person instructions and will be additionally contacted *via* phone to ensure a smooth process and proper implementation of the light therapy.

Participants take light therapy at home; however, the variability in the specific implementation details of the treatment, particularly among subjects with poor adherence, poses potential challenges to the trial’s overall outcome. To mitigate these concerns and enhance the integrity of the study, adherence to the treatment protocol in both groups is monitored using an eye-tracking system. This system documents each participant’s active usage time, ensuring a comprehensive assessment of treatment adherence.

A treatment blinding test will be administered to the participants at day 42. The treatment blinding test assesses the participant’s awareness of which treatment group, he/she was allocated to for assessment of blinding efficacy. In addition, an evaluation of participants’ expectations regarding the effectiveness of the treatment will be systematically conducted at the initial visit, serving as a baseline measure.

An independent investigator will program 30 active treatment and 30 placebo devices in total assigned with labels A and B to the device identification numbers. The statistician creates unequal randomization blocks (e.g. ABBA, BAABBA) where he assigns a patient number (e.g. FELIX01, FELIX02) to the treatment group (A or B) and then the treatment group to a random device (corresponding to the group). The block size is blinded to investigators.

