### Invisible spectral flicker and light characteristics

A light device that delivers a 40 Hz light stimulus (OptoCeutics) will be used in the study. Unlike stroboscopic light, the device introduces the flickering stimulus by alternating between two color combinations (Figure 2). Alternating between two white light sets makes the flickering almost imperceivable to the human eye, therefore reducing discomfort related to stroboscopic or flashing light.

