### Data collection

Identifiable data such as full name, address, and social security number will only be shared with key personnel and only for data collection from the electronic patient journal. All data sharing will be according to the European General Data Protection Regulation (GDPPR) and in agreement with permission from the Danish data protection agency. The REDCap system is used for collecting data during patient visits. The only data collected outside of the investigational site is the average usage time of the device, which is stored locally on the device and does not include any personal information. Depression severity measures (HAM-D_17_) will also be collected from the patients that dropped out.

Data collected: Age, gender, social security number, e-mail, phone number, inclusion date, diagnosis, sociodemographic data (residential status, work situation, somatic condition, prior and current depressive episode, smoking, eliciting factors for depressive episodes, suicidality history, alcohol, drug abuse), medical history, depression, mania, quality of life, sleep, side-effect, and suicidality ratings, treatment expectancy, blinding and treatment evaluation, concomitant medication.

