### Statistical analysis plan

The analysis will be carried out using R software version 4.2.1 or higher (Free Software Foundation’s GNU General Public License). With a minimal clinically important difference of 3 points on the HAM-D_6_ scale, an expected standard deviation of 3.5, an alpha value of 0.05, and a power of 90%, and considering dropout, we will need a total of 60 patients to show the significance of the primary outcome. Based on the previous studies at Psychiatric Centre Copenhagen, dropout is expected to be below 25%, and we will attempt to administer the HAM-D_6_ (primary endpoint) for all the patients who drop out of the trial. An intention-to-treat population, including all randomized participants, will be used for analyses. The mean change from baseline to post-treatment at day 42 in HAM-D_6_ scores will be compared between treatment groups using a two-sample *t*-test. *T*-test assumptions of normality and equal variance will be checked. A mixed model repeated measures method will be used to analyze depression symptoms from baseline to measurements at day 7, day 21, day 42, and day 56. The Benjamini-Hochberg correction will be used for multiple comparisons. A *p*-value of less than 0.05 is considered a rejection of identity between groups.

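### A report that interferes with blinding is a drop-out criterion, yet the only blinding test is at day 42, so known blinding failures can leave before blinding is measured

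*Protocol article*

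**What the plan says.** All of this is in the protocol article.

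- **Drop-out criteria** (Study design and interventions, below Figure 1). After several clinical items, the list closes with "and patients reports conditions treatment that interfere with blinding". The phrase is ungrammatical, and what counts as such a report is not explained.
- **Blinding test** (Study design and interventions). "A treatment blinding test will be administered to the participants at day 42". No other time is named. Treatment expectancy is also recorded at the initial visit, but that is an expectation of benefit and not a guess of allocation.
- **What differs between arms.** The active light flickers at 40 Hz and the placebo light is continuous. The section on invisible spectral flicker says that switching between two sets of white light "makes the flickering almost imperceivable to the human eye". The masking is thus described as nearly, not fully, complete.
- **Data from drop-outs.** Data collection: "Depression severity measures (HAM-D_17_) will also be collected from the patients that dropped out". Statistical analysis plan: "we will attempt to administer the HAM-D_6_ (primary endpoint) for all the patients who drop out of the trial". Neither mentions an allocation guess at exit or says when the rating is taken.
- **Analysis set** (Statistical analysis plan). Intention to treat, with all randomised participants. The primary analysis is a two-sample t-test on the HAM-D6 change to day 42.

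**The concern.** The exit rule and the timing of the blinding test work against each other. A patient who says something that shows the blind has failed meets a drop-out criterion. The blinding test comes at the end of treatment. If it is answered only by those still attending, the clearest failures have been filtered out, and the result that should support the double-blind claim looks better than the blinding was.

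The rule also makes leaving the trial depend on an event after randomisation that may be linked to the allocated light. That matters for the primary comparison wherever a leaver ends up without a day-42 HAM-D6. The rule serves blinding rather than patient safety, so it can be changed without touching the clinical items in the list.

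**Working it through.** The article gives no figure for unblinding and no dropout by arm or cause, so there is no stated figure to reproduce. The calculations below are illustrations, and their assumptions are marked.

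**Inputs from the article:** 30 active and 30 placebo devices; target difference 3 points on HAM-D6; SD 3.5; alpha 0.05; all-cause dropout expected below 25%.

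**Assumptions:** *k* of 30 patients in an arm become sure of their allocation, report it and leave before day 42 (*k* = 3, 6 or 9, i.e. 10%, 20% or 30%); everyone else guesses 50:50; leavers are not asked for a guess.

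**1. Effect on the blinding test**

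Proportion of correct guesses among all randomised in the arm: p = (k + (30 − k)/2)/30 = 0.5 + k/60. Blinding index = 2p − 1 = k/30.

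| k | p, all 30 | Index, all 30 | Number tested at day 42 | p, tested | Index, tested |
|---|---|---|---|---|---|
| 3 | 55% | 0.10 | 27 | 50% | 0 |
| 6 | 60% | 0.20 | 24 | 50% | 0 |
| 9 | 65% | 0.30 | 21 | 50% | 0 |

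The calculation is done within one arm. With k = 3 in both arms, the index falls from 0.10 to 0 in both, so the distortion needs no imbalance between arms. Unblinded patients who do not report it stay and are tested, so the table shows the largest distortion for each k.

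**2. Effect on the primary comparison, only for leavers without a day-42 rating**

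Let a fraction f of the active arm leave without a rating, and let their mean change differ by d from that of the rest. The mean of those remaining then differs from the mean of all randomised active patients by f × d. Assume d = 2 points:

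- f = 10%: 0.1 × 2 = 0.2 points, and 0.2/3 = 7% of the target difference.
- f = 30%: 0.3 × 2 = 0.6 points, and 0.6/3 = 20% of the target difference.

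The direction depends on the sign of d, which the article does not inform. Where every leaver is rated at day 42, the shift from this source is 0.

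The upper end is demanding: 9 of 60 is 15% of all randomised patients lost to this one cause, when dropout from all causes is expected to stay below 25%, i.e. below 15 patients.

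**3. Precision**

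With 30 rated patients per arm, a two-sided t-test (sidedness assumed) has 90.4% power for 3 points at SD 3.5. Losing the rating of 6 or 8 active patients lowers this to 86.7% or 85.0%.

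**The case against.** The case against a stronger reading is good, and most of it stands.

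- **A reader might infer that the primary comparison is biased.** The article does not support that as a general statement. All randomised patients are in the analysis and HAM-D is sought from those who leave, so dropping out does not by itself remove a patient from the primary result. What remains is narrower: the rating is only attempted, and the article does not say it will be taken at day 42. A rating at exit is not a change to day 42.
- **A reader might infer that the leavers come mainly from the active arm.** This is plausible, since only that light flickers, but no perception rate is given and the article describes the placebo as closely matched. The garbled criterion could also cover a patient who describes the treatment to an assessor, which can happen in either arm. A placebo patient might also draw conclusions from seeing no flicker, because the EEG procedure uses a 40 Hz strobe at baseline.
- **The article does not say that drop-outs skip the blinding question.** True. The full protocol may contain an exit visit. Still, where the article lists what is collected from drop-outs, it names HAM-D only, and it fixes the blinding test at day 42.
- **Day 42 is a sensible time to ask, and assessors do not see the devices lit.** Also true. The problem is not that day 42 is used, but that the exit rule acts before it.

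None of this answers the selection of who takes the blinding test.

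**Conclusion.** The point holds for the blinding assessment. As written, the plan lets patients known to be unblinded leave before the only blinding test, so a day-42 result in those who remain can overstate blinding success. In the illustration, an index of 0.10 to 0.30 is reported as 0. That rests on the assumptions that all such patients report and leave, that they give no guess at exit, and that the others guess at random. It does not rest on unequal reporting between arms.

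For the primary comparison the risk is conditional. More frequent exits from the active arm are possible but not shown. A shift of 0.2 to 0.6 points arises only if 10% to 30% of that arm leave without a day-42 rating and differ by 2 points from the rest, none of which the article states. The change is worth making because it alters a stated rule at very little cost.

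**What to change.** 1. Reword the last drop-out item so that it is clear what kind of report is meant, and remove a blinding report as a reason to leave the trial. The clinical items in the list are not affected.
2. Record the report with its date and content. Keep the patient in scheduled follow-up, with HAM-D6 at day 42, and in the intention-to-treat analysis.
3. Take the allocation guess, with the reason for it, at any early exit as well as at day 42.
4. Report the guesses by arm for all randomised patients, with the number who reported being unblinded and the number with no guess.

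Cost: a change of protocol wording and one extra question at exit. The downside is that some patients known to be unblinded stay in the trial; the recorded reports at least make their number visible by arm. A further guess earlier in treatment, or a guess by the HAM-D rater, is optional and not needed to settle this point.

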### Invisible spectral flicker and light characteristics

A light device that delivers a 40 Hz light stimulus (OptoCeutics) will be used in the study. Unlike stroboscopic light, the device introduces the flickering stimulus by alternating between two color combinations (Figure 2). Alternating between two white light sets makes the flickering almost imperceivable to the human eye, therefore reducing discomfort related to stroboscopic or flashing light.

**Figure 2. F0002:**
[figure not shown]
Representation of light paradigms and the design of invisible spectral flicker. Set 1: Cyan and red, set 2: blue and yellow.

A traditional bright light therapy approach introduces app. 10k lux at the distance of 30 cm for 30 min or 2.5 k lux at 30 cm for 1 h [4]. The light used for the study emits <1500 lux at 30 cm and is not intended for the treatment of seasonal affective disorder (SAE) or as an alternative for bright light therapy. However, the light uses a wide spectrum of colors, including shorter wavelength cyan and navy blue, which are known to have a greater effect on the circadian system.

Melanopic Equivalent Daylight illuminance (mEDI) is an essential measure in light therapy studies and for quantifying the biological impact of light on the human visual system. The measure represents the melanopsin-weighted stimulus received by the intrinsically photosensitive retinal ganglion cells (ipRGCs) in response to light exposure. These specialized cells are responsible for conveying non-visual light information to various parts of the brain, including the suprachiasmatic nucleus (SCN), which regulates the body’s circadian rhythms. The ipRGCs are particularly sensitive to short-wavelength (blue) light and play a crucial role in regulating various physiological processes, such as the sleep-wake cycle, alertness, mood, and hormone production [35–37].

Measuring the mEDI in our study is essential as it controls for the potential effects of light on the circadian system and associated physiological responses, such as improved mood or quality of sleep. Both white light paradigms used in the study (masked flickering light and placebo continuous light) should have the same effects on the circadian system to compare the isolated effects of 40 Hz stimulation. [38] The light characteristics of both treatment conditions are described in (Table 2).

**Table 2. t0002:** Light matching in two different treatment conditions.

Group	CCT [K]	u’	v’	Radiant intensity [W/sr]	α-opic EDI metrics [lx]				
					Melanopic	Cyanopic	Chloropic	Erythropic	Rhodopic
Active	3.186	0.2478	0.5061	0.3522	**292**	180	325	383	308
Placebo	3.197	0.2479	0.5046	0.3624	**300**	186	327	384	315

CCT: Correlated Color Temperature (Kelvin), u’ and v’ are chromaticity coordinates used to describe the color of light. EDI: Equivalent Daylight Illuminance. Field of view/angle of the measurement device is 2°. Measurements are made at 50 cm distance.

## Study assessments and endpoints

Study assessments include questionnaires pertaining to the symptoms of depression, and include the assessment of depression severity, suicidal ideation, cognition, sleep duration and quality, general quality of life and mania. Summary of study evaluations and endpoints can be found in (Table 3).

**Table 3. t0003:** Summary of study endpoints.

	Endpoints	Description
Primary	Hamilton Depression Rating Scale 6 (HAM-D_6_) Time points of measurement: baseline, day 7, day 21, day 42, and day 56. The primary endpoint is the mean difference in scores between treatments at baseline and day 42.	The scale is designed to rate the severity of depression in patients by a healthcare professional. The assessment scale contains 6 items pertaining to the symptoms of depression experienced over the last three days. The score ranges from 0 to 24 [0–4] = no depression [5–6] = subclinical depression [7–8] = mild depression [9–11] = moderate depression [12–22] = moderate-severe depression A 2–3-point change in score is considered a minimum clinically important difference (MID) [39,50].
Secondary	Major Depression Inventory (MDI) Time points of measurement: baseline, day 7, day 21, day 42, and day 56	MDI is a depression self-assessment questionnaire. It consists of the 10 ICD-10 symptoms of depression. The sum of 10 questions indicates the degree of depression. The score ranges from 0 to 50 <21 = normal [21 − 25] = mild depression [26–30] = moderate depression ≥ 31 = severe depression [41]
	Neurocognitive battery Time points of measurement: baseline, day 7, and day 42	Assessing attention and recognition of emotional facial expressions using Facial Expression Recognition Test (FERT) and self-referent memory for emotional words using the Emotional Categorization and Memory test (ECMT). Non-emotional cognition is investigated with the Screen for Cognitive Impairment in Psychiatry (SCIP) and the Trail Making Test B (TMT-B) [51,52].
	Sleep diary covering last 7 days. Time points of measurement: continuous, by subjects themselves	Average last 7 days’ sleep parameters: Duration, falling asleep and waking up times, sleep quality, daytime sleep.
	Pittsburg Sleep Quality Index (PSQI) Time points of measurement: Baseline, and day 42	Seven component scores are derived, each scored 0 (no difficulty) to 3 (severe difficulty). The component scores are summed to produce a global score (range 0–21). Higher scores indicate worse sleep quality [53].
	WHO quality of life index (WHO-5) Time points of measurement: Baseline and day 21, day 42, and day 56	The score ranges from 0 to 25, with 0 representing the worst possible and 25 representing the best possible quality of life. To obtain a percentage score ranging from 0 to 100, the raw score is multiplied by 4. A percentage score of 0 represents the worst possible, whereas 100 represents the best possible quality of life. A 10% difference indicates a significant change [54].
Safety	The UKU Side Effects Scale Adverse Event (AE) Report Form The safety endpoint is the presence or absence of any adverse events during the treatment period.	All device-related adverse events will be reported and analyzed throughout the treatment and follow-up periods [55].
	Suicidal Ideation Attributes Scale (SIDAS) Time points of measurement: baseline, day 7, day 21, day 42, and day 56	The scale consists of 5 items: frequency, controllability, closeness to attempt, level of distress, and impact on daily functioning. Items are measured on a 10-point scale. The total score ranges from 0 to 50 (50 = worst). A cut-off of 21 may indicate a high risk of suicidal behavior [56].
	Young Mania Rating Scale (YMRS) Time points of measurement: Baseline, day 7, day 21, day 42, and day 56	The Scale assesses the manic symptoms that the light therapy could induce. The scale has 11 items and is based on the patient’s subjective report on his/her clinical condition over the last 48 h. Core mania symptoms include elevated mood, increased motor activity, irritability, and aggressive behavior. The Young Mania Rating Scale total score ranges from 0 to 60, where higher scores indicate more severe mania [57].
Adherence	The eye-tracking function of the device	Average device usage in minutes per day will be calculated. High adherence is considered 70% of the recommended duration of 1-h treatment per day.

### Assessment of depression severity

Hamilton Depression Rating 17 item (HAM-D_17_) and its subscale (HAM-D_6_) – is an interviewer-administered scale for rating the severity of depression. The HAM-D_6_ scale is a subscale of the HAM-D_17_ that has shown superior psychometric properties [39,40] and includes 6 items from the original scale, including depressed mood, work and activities, somatic symptoms, psychic anxiety, guilt, and psychomotor retardation. The HAM-D_6_ scale is rated for the last 3 days. The score range for the full scale is 0–52 and from 0 to 24 on the subscale, and the subscale scores between 9 and 11 are considered moderate depression, and scores above 11 – moderate-severe depression.

Major depression inventory (MDI) will be used as a self-report measure of depression severity. Patients will evaluate their depression symptoms at baseline and during every follow-up visit. The inclusion criteria for this study is an MDI score of 21 or above [41].

### Cognitive evaluation

It is hypothesized that antidepressant drugs reverse negative bias in the cognitive processing of emotional information [42]. This effect has been shown to occur early in the course of antidepressant drug treatment and predicts treatment response [43]. Therefore, in this RCT, we investigate for the first time whether 40 Hz masked flickering light therapy produces a similar early shift in the cognitive response to emotional information in depression and whether this early change is related to treatment efficacy. We will also investigate whether 40 Hz mask flickering light improves non-emotional cognitive functions in parallel with its effects on depressive symptoms.

The neurocognitive test battery assesses emotional and non-emotional cognition. The recognition of emotional facial expressions will be assessed using the Facial Expression Recognition Test (FERT) and self-referent memory for emotional words using the Emotional Categorization and Memory Test (ECMT) [44]. Non-emotional cognition will be investigated with the Screen for Cognitive Impairment in Psychiatry (SCIP) [45,46] and the Trail Making Test A and B (TMT-A and TMT-B) [47]. SCIP is a well-evaluated screening instrument for examining cognitive performance in psychiatric patients and includes list learning, consonant repetition, verbal fluency, delayed list learning, and visuomotor tracking tests [48]. TMT is a short additional test that evaluates visual attention (part A) and attention switching (part B; executive function), respectively.

